## 5. Data Security and Protection of Subject Confidentiality

- a. Are you applying for a Certificate of Confidentiality? No.
- b. Identify the data security plan below that best describes how you will minimize the risk of a breach of confidentiality by checking one of the boxes on the left side of this chart. If your study includes sequential phases that require different procedures, or does not fit these categories, explain in "Other".

*Note: Identifiers include name, address, SSN, hospital record number, etc., and other indirect identifiers (e.g., date of birth) that, when combined with other variables, may make a subject identifiable. These categories reflect minimal standards; you may impose more stringent protections. See the JHSPH Data Security Guidance at [www.jhsph.edu/irb](http://www.jhsph.edu/irb) > Policies & Guidance > Guidance for additional information regarding best practices.*

**Hard Copy of data collection form: Indicate your choice but typing an X in the appropriate box on the left:**

|   |                                                                                                                                                                                                                                                                                                                                 |
|---|---------------------------------------------------------------------------------------------------------------------------------------------------------------------------------------------------------------------------------------------------------------------------------------------------------------------------------|
|   | Hard copies of data collection materials have identifiers and are locked in a secure cabinet or room with limited access by specified individuals. When possible, redacted (de-identified) versions of the data collection sheets will be used for coding and analysis.                                                  |
| X | Hard copies of data collection materials include an ID code and do not have personal identifiers . However, a code linking the data to the subject's personal information is stored separately from the data collection sheets, and is locked in a secure cabinet or room with limited access by authorized individuals. |
|   | Data are not collected on paper.                                                                                                                                                                                                                                                                                                |
|   | Other (describe):                                                                                                                                                                                                                                                                                                               |

**Electronic Databases: Indicate your choice by typing an X in the appropriate box on the left: :**

*Note: A de-identified version of the database should be used for data analysis except in instances in which identifying information is prerequisite for coding or analysis. Databases that retain identifying information require a higher degree of electronic security.*

|  |                                                                                                                                                                                                                                                                                                                                                   |
|--|---------------------------------------------------------------------------------------------------------------------------------------------------------------------------------------------------------------------------------------------------------------------------------------------------------------------------------------------------|
|  | The study is minimal risk and data collected are not sensitive in nature. No personal identifiers are included in the electronic database. Any electronic documents that link IDs to identifying information are stored on a computer in accordance with JHSPH Data Security guidance.                                                     |
|  | Personal identifiers are included in the database. The data are stored on a computer that is password protected with a secure server. Transfer or storage on portable devices (e.g., laptops, flashdrives) is encrypted. The devices on which this information is stored are accessible only to individuals who need access to these data. |
|  | No personal identifiers are included in the database but linkable identifiers exist separately and the data are sensitive in nature (e.g., substance use, mental health, genetic propensities, sexual                                                                                                                                      |

|   |                                                                                                                                                                                                                                                                                                                                                                                                                                                       |
|---|-------------------------------------------------------------------------------------------------------------------------------------------------------------------------------------------------------------------------------------------------------------------------------------------------------------------------------------------------------------------------------------------------------------------------------------------------------|
|   | practices or activities ) such that disclosure could provide a risk to the individual. The codes are stored on a computer that is password protected with a secure server. Transfer or storage on portable devices (e.g., laptops, flashdrives) is encrypted. The devices on which this information is stored are accessible only to individuals who need access to these data.                                                                |
| X | No personal identifiers are included in the database but linkable identifiers exist separately and the data are sensitive in nature ( e.g., substance use, mental health, genetic propensities, sexual practices or activities ) such that disclosure could provide a risk to the individual. Information linking personal identifiers to ID codes of subjects entered into the database is stored separately on paper and locked away. |

- c. *If you are using participants' personal identifiers, describe any plans for disposing of identifiers including if, when and how that will be done.*

As part of a client monitoring process, the client's name, address and contact information will be maintained by the counselors and kept separate from study forms. For purposes of all data collection being carried out by counselors (pre- and post-intervention assessments and client monitoring forms) an assigned client ID number will be used. The Project Director, Field Project Coordinator, and Field Project Manager will keep a list of all the names, contact information and ID numbers. Clinical supervisors and counselors will have names, contact information and ID numbers only for the clients with whom they are working directly. The master list and all of the assessment forms will be kept securely under lock and key with access only by the research team.

Collection of identifiers is necessary to allow the counselors to keep track of their clients and in order to link the results of the screening interview with the repeat interview done after the intervention is completed. Only by having the personal identifiers linked to the code can we ensure that both interviews are with the same person. This is also necessary in that we do not plan to have the repeat interview carried out by the counselor providing the intervention to a given client but by another counselor participating in the study. At the end of the study (after completion of analysis comparing baseline and follow-up results) the lists that the supervisors made that connect study forms with client information will be destroyed. All other forms will be kept per local organizational protocols for their own service files.

- d. *Describe any plans for destroying data including if, when and how that will be done.*

The original screening and intake/assessment instruments will be kept in the BBP office in Mae Sot. Electronic records will be stored on a single, secure computer and on the PI and co-PI's computers and on a separate hard drive. Data from the baseline and follow-up interviews as well as some tracking data of client participation will be transferred to JHU via encrypted data files and stored at JHU in a password-protected computer in a locked office. Electronic copies of data will not be destroyed.

## 6. Recruitment process:

- a. *Describe how participants will be recruited.*

As with the previous qualitative and validity studies, we will work with the local counterpart organizations to encourage members to present themselves for screening. Persons who are otherwise seen by counselors and other organization staff-members during their regular work will also be encouraged to provide their contact information for follow up.

- b. *Explain how your recruitment materials will be used.*

Local partner organizations (BBP, AAPP, MTC and SAW) have developed a one-page handout and pamphlet in the local language (Burmese) that provides a brief description of the project and contact information for persons in the project whom they can contact for more information. These contact persons with the local partner organizations will then collect names and contact information for those who express interest in possibly taking part in the study..

- c. *If relevant, address any privacy concerns associated with the recruitment process.*

Based on our previous studies using the same approach, we do not have any privacy concerns for the recruitment process as this step will involve conversations with program providers known and trusted in the community. Staff-members from the participating organizations have been made aware throughout the course of the study that they are not to share publicly any information about individuals who may contact them out of interest in participating in the study and in the CBI intervention.

## **7. Consent process and documentation:**

- a. *Describe who will obtain informed consent from participants, and how, when and where consent will be obtained.*

Prior to the screening process and intake interview, the counselor will verbally consent participants, informing them of the interview process, the intervention therapy, the re-interview process and the possible risks and benefits of participation. The interview will take place at a private location convenient to the potential client and could include the BBP, AAPP, SAW, or MTC offices or a private home. At the beginning of the consent process, the counselor will establish that the person meets eligibility criteria for inclusions—that is, they are 18 years or older, a Burmese national, and resident in the Mae Sot area. During the oral consent process, the potential client will be informed that they will first be asked a series of screening questions to assess their mental health symptomology. If the person is determined to be eligible for inclusion in the intervention study on the basis of these higher symptom scores, they will be told that they will be randomized into a case group or wait-control group and informed that they will either start the intervention within approximately one week or will be asked to wait several months. Following the intervention, both groups will be re-interviewed.

Thus the screening consent form will offer a recruited individual to consent to be screened for trauma exposure and for depression and trauma symptoms only. If the individual is deemed eligible for inclusion, the study consent form will offer the potential client an opportunity to complete the intake/assessment interview and to be randomized into a case or wait-control group for treatment (for the case group), and a follow-up interview several months later. For those in the wait-control group, they will be further asked if they are willing to be contacted once a month by the counselor while they are waiting for the follow-up interview.

Failure to show up for first session will disenroll a person from the study; we do not regard a client as fully consented unless they show up for Session 1 as they may have changed their mind after discussing participation with family members. If a client clearly (in the view of the counselor, clinical supervisor and study team) does not have mental capacity to give consent, then that person would not be asked to be in the study.

- b. *If the study will involve vulnerable populations (e.g., children, prisoners, cognitively impaired adults, non-English-speakers, etc.) describe efforts to ensure their understanding*

*of the research and the extra protections that will be in place to ensure their voluntary participation.*

No specific vulnerable populations (beyond the designation of survivors of torture) will be enlisted in the study. All intervention materials and counseling sessions will be in Burmese.

- c. If a waiver of consent or a waiver or alteration of signed consent is requested, provide a justification for the waiver/alteration, and describe any alternate procedures for informing participants about the research.*

A waiver of signed consent is being requested. Given the sensitive nature of signing documents among this population, we will have the counselors read an oral consent script, both for the screening interview and, if eligible, for study participation. Whether the client gives verbal consent or declines, the counselors will sign the consent script form, indicating the client's decision; this form will then be kept on file for the duration of the study.

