Starting in June 2011, the counselors trained in CBI will begin to implement this intervention with the clients that come to see them as part of the ongoing services provided by AAPP, SAW, and MTC. A practicum round of the CBI intervention began shortly following the CBI training in order to be sure that counselors and supervisors are properly trained in the intervention. The research study will begin in June 2011 when approximately 400 people will be screened into the intervention (for a final sample of 300); approximately half of these would be randomly assigned to the “case” group, to begin the intervention immediately after screening while the other half would be assigned to the “wait-control” group to receive CBI after the “case” group has completed the CBI intervention.

The proposed study will be embedded within the ongoing MTC, SAW and AAPP programs which could include non-specific counseling services, social services and support and, in the case of Mae Tao clinic, medical assistance. That is, we are proposing to study the effectiveness of these intervention strategies in a subset of the clients the organizations serve. The organizations will continue to provide services, as space allows, to anyone who seeks their services regardless of whether they meet eligibility for our proposed study. However, those who meet our inclusion criteria will be invited to participate in the research component of the service program.

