*Training on Consent and Screening Procedures:* We plan to begin the actual intervention study with CBI in June 2011 (corresponding to Month 5 in the table below). Prior to that, JHU study faculty will provide training to all counselors and clinical supervisors on how to carry out consent and screening procedures, including administering the study consent form and interpreting depression and trauma severity scores.

*Screening:* A screening process, and allocation to either an intervention (case) group or temporarily to a wait-control group, will continue until the practicum round of CBI training has been completed in late June or early July. If a sufficient number of clients for the intervention group are not identified by early July, screening and enrollment could continue beyond that time.

*Service Provision:* Beginning in late June or early July 2011, the intervention will begin with weekly sessions provided by the counselors to the client and with supervision provided in the form of weekly meetings between the counselor and clinical supervisor and in the form of weekly phone conversations between the clinical supervisors and the JHU trainers/clinical psychologists. Both intervention and control clients will be monitored using separate client monitoring forms. These forms will include information on the clients' well-being, any treatment or medication they are receiving, and whether or not the client's are in danger to themselves or others. Clients who are in danger of committing suicide will be discussed immediately with supervisors, or referred if supervisors are not immediately available. There is a Safety Plan (see attachment) in place for this project that includes a response team of the following: the counselor, the counselor's clinical supervisor, a medical doctor who is part of the project team, and the Field Project Coordinator. The Project Director will provide support for this response team at all times and will be in regular contact with the Project PI. A copy of the Safety Plan protocol is included in the IRB application.

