Persons who are in the intervention group or the wait control group whose depressive symptoms worsen (but not to the point of ineligibility) would first be evaluated by the counselor in conjunction with the study's clinical team and with the CCT medical monitor. Based on this assessment, a decision could be made to continue CBI treatment alone or the client could be provided referral to standard of care treatment possibly including non-specific counseling. This treatment would be recorded in the client monitoring records.

We should note that some of the counselors who will deliver the CBI intervention are also qualified to provide other services (for example, some of the Mae Tao Clinic counselors providing the intervention also work at the Counseling Center on a part-time basis). We will ask for the period of the intervention, that the CBI counselors provide only CBI to their study clients. If referrals are made for other services (or clients independently seek other services including,

possibly, non specific counseling) these other services would be provided by someone other than the CBI counselor.

|                                                               | Month |    |    |    |    |    |    |    |    |    |    |    |
|---------------------------------------------------------------|-------|----|----|----|----|----|----|----|----|----|----|----|
|                                                               | 1     | 2  | 3  | 4  | 5  | 6  | 7  | 8  | 9  | 10 | 11 | 12 |
| 1. Training on CBI Method                                     | XX    | XX |    |    |    |    |    |    |    |    |    |    |
| 2. Practicum Round on CBI                                     |       |    | XX | XX | XX |    |    |    |    |    |    |    |
| 3. Recruitment                                                |       |    |    | XX | XX |    |    |    |    |    |    |    |
| 4. Screening and Baseline Interviews of Case and Wait-Control |       |    |    |    | XX | XX |    |    |    |    |    |    |
| 5. Intervention (Case Group)                                  |       |    |    |    |    | XX | XX | XX | XX | XX |    |    |
| 6. Follow-up Interviews (Case and Wait-Control Groups)        |       |    |    |    |    |    |    |    |    | XX |    |    |
| 7. Intervention for Wait-Control Group                        |       |    |    |    |    |    |    |    |    | XX | XX | XX |

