Persons in the wait-control group will be instructed to contact their counselor, either by phone or in person, if their symptoms worsen during the wait period. The Field Program Coordinator will work with the counselors to coordinate a process of check-in (either in person or by phone) with wait-control clients every month for assessment of symptom severity by the counselors. In cases where the symptoms are worse, this will be reported to the clinical supervisors and the JHU study team and a decision made about whether the participant should be referred for additional services. In severe cases where the person is a risk to themselves or others the project will follow the Safety Plan (explained above).

*8) Explain and justify whether there will be blinding.*

In this study, the follow-up interviews of the case group clients will be carried out by counselors different from those who provided the CBI treatment. Follow-up interviews will be randomly assigned to counselors who will be blind to the initial assessment scores of the interviewee and who would not have knowledge of a client's results during the CBI intervention. This will eliminate risk of bias on the part of counselors who might wish to improve the outcome scores of their client caseload and would promote rater independence between the pre- and post-intervention measures.

*9) Explain and justify whether participants will not receive routine care or will have current therapy stopped*

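### The start of CBI told to case participants at consent (about one week) does not agree with the protocol's own schedule, which allocates from June but opens case sessions only in late June or July

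*Protocol*

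**What the plan says.** **Start of treatment, as told or described.** Section 7a (consent) has participants informed that "they will either start the intervention within approximately one week or will be asked to wait several months". Section 2 describes the case group as assigned "to begin the intervention immediately after screening". Section 4, items 1 and 7 also speak of immediate treatment.

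**Start of treatment, as scheduled.** Section 2: "The research study will begin in June 2011 when approximately 400 people will be screened into the intervention". Section 4, item 2 equates June 2011 with Month 5 of the timetable and says that screening and allocation "will continue until the practicum round of CBI training has been completed in late June or early July". Under Service Provision it then says: "Beginning in late June or early July 2011, the intervention will begin with weekly sessions provided by the counselors". In the timetable, the practicum (row 2) occupies Months 3 to 5, screening and baseline interviews (row 4) Months 5 and 6, and the case-group intervention (row 5) Months 6 to 10.

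**Contact while waiting.** The randomization text in section 4, item 7 tells wait-control clients to contact their counselor if symptoms worsen, and sets up a check-in "with wait-control clients every month for assessment of symptom severity by the counselors". Item 3 also lists monthly contacts for that group only. For case clients, the safety questions (section 8b) and symptom assessment (section 11a) are attached to treatment sessions.

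**Missing Session 1.** Section 7a disenrols anyone who does not attend the first session. Section 4, item 5 includes all eligible enrolled participants in an intent-to-treat analysis.

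**The concern.** A participant allocated to the case group early in the screening period is given a start date that the schedule may not be able to meet. Three things are at stake.

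- **Accuracy of consent.** The interval is read aloud, under an oral script, to symptomatic survivors. It should be one that the schedule can deliver.
- **Losses in one arm.** Wait-control clients have no Session 1 until after their follow-up interview, so during the comparison period the disenrolment rule can act only on case clients, after they know their allocation. A longer gap gives more time for such losses, and these sit badly with the intent-to-treat statement.
- **Unspecified contact.** Between allocation and Session 1, the protocol sets out no contact schedule for case clients, while it does set one for waiting controls.

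**Working it through.** The stated figure is about one week (7 days) from consent to first session. It can be checked only by calendar arithmetic.

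**Month mapping.** June 2011 = Month 5 (section 4, item 2), so Month 1 = February and Month 6 = July. This agrees with training in February-March (section 2; Months 1-2) and recruitment from May (section 4, item 2; Month 4). On the timetable, row 4 is therefore June-July, row 2 ends in June, and row 5 starts in July. The text allows a slightly earlier session start, in late June.

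**Assumptions.** The protocol gives no days. I take screening to open on 1, 8, 15 or 20 June, and sessions to start on 20 June, 25 June, 1 July or 10 July.

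**Formula.** Longest wait = first session date − date screening opens.

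| Screening opens | Sessions from 20 June | 25 June | 1 July | 10 July |
|---|---|---|---|---|
| 1 June | 19 days | 24 | 30 | 39 |
| 8 June | 12 | 17 | 23 | 32 |
| 15 June | 5 | 10 | 16 | 25 |
| 20 June | 0 | 5 | 11 | 20 |

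The range is 0 to 39 days. The one-week figure holds for the earliest enrolees in only three of the sixteen combinations (5, 0 and 5 days), those in which screening opens no more than a week before sessions. The protocol does not state that condition. With the timetable's earliest start, 1 July, anyone allocated before 24 June waits more than 7 days (1 July − 24 June = 7).

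**Effect on the follow-up limit.** Section 4, item 2 puts the follow-up interview no more than 3 to 4 months after enrolment. Ten weekly sessions span 9 × 7 = 63 days from first to last. In the worst case, 39 + 63 = 102 days. From 1 June, three months is 92 days and four months is 122, so the course can run past three months but ends inside four.

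**Effect on contacts.** Control check-ins are monthly. Over a gap of at most 39 days, a control client would have about one.

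**The case against.** The strongest reply is that the inconsistency is one of scheduling text and that its consequences are easily overstated. Most of this stands.

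- **Length of the wait.** A reader might infer that early enrolees wait 23 to 37 days, or that about 38% of the case arm (57 of 150) waits more than a week. The first needs screening to open on 1 June, with sessions starting 24 June to 8 July. The second needs even enrolment over the 61 days of June and July with sessions from 1 July (23/61 = 38%). The protocol gives neither an opening day nor an enrolment rate, and a timetable in whole months cannot support day-level waits. Section 2 also has counselors implementing CBI from June, so the late start is itself not settled.
- **Monitoring.** A reader might infer that case clients are left with no planned contact, or are monitored materially less than controls. That is too strong. Section 4, item 2 provides monitoring forms for both arms and evaluation of worsening depressive symptoms in either group. Item 13 covers anyone found in active danger at screening or during the study. Section 8b offers a further visit to people still distressed by the interview. A monthly check-in would add about one contact at most. What remains is that none of these provisions sets a schedule before Session 1, and the instruction to call is written for controls only.
- **Bias and follow-up.** A reader might infer that the delay biases the comparison or breaks the follow-up limit. Baseline is taken around randomization in both arms and follow-up timing is common, so the delay itself would at most dilute the effect. The four-month limit is not exceeded.
- **Stale risk assessment.** Symptoms and safety are assessed at every session, including the first, so an outdated assessment would not go unnoticed once treatment starts.

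The reply does not remove the contradiction. The June implementation statements add a further conflict within the schedule.

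**Conclusion.** The point holds as an internal contradiction. The interval told at consent and the immediate start in section 2 cannot both agree with section 4, item 2 and timetable rows 2, 4 and 5 for anyone allocated more than a week before sessions open. The contradiction is certain but its length is not: the longest wait lies between 0 and 39 days under the assumed opening and start dates, and the number of participants affected cannot be estimated from the protocol.

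The practical weight comes from a figure given to participants that the schedule may not honour, and from a gap confined to the arm in which a missed first session leads to disenrolment. The tension between that rule and the intent-to-treat statement exists whatever the dates; a longer gap only gives it more room to act. The documents do not support a claim of absent monitoring, a biased comparison or a breached follow-up limit.

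**What to change.** Reconcile section 2, section 4 item 2 (Screening and Service Provision), timetable rows 2, 4 and 5, and section 7a, so that the opening of allocation, the first case session and the interval told at consent agree. Section 4, item 2 already allows enrolment to run past early July, which leaves room to do this. If allocation before sessions open is kept, correct the interval told to participants, and reconcile the contact wording in section 4, item 7, now written for wait-control clients only, with the both-arm monitoring statement in item 2. Which start or contact arrangement is right is for the investigators.

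The cost is a timetable and wording change, with no extra participants or staff. Allocation may open somewhat later, which could push back the wait-control phase and the December 2011 end in section 4, item 4. There is little slack: on the same month mapping, timetable row 7 already runs to Month 12, January 2012.
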